#### Primary Infant Assessments

The mother will record infant sleep for 1 week per month in the baby’s day diary [46]. Boxes are filled in daily for 1 week with symbols that correspond to when the infant is asleep, awake, awake and fussy, sucking, or feeding. This measure has been widely used and exhibits desirable reliability and validity [47,48]. The Brief Infant Sleep Questionnaire [40] is used to assess the infant’s sleep during the past week. The Infant Behavior Questionnaire-Revised [49] will be used to allow mothers to report, on a 7-point scale, the frequency with which infants have enacted specific behaviors in common situations during the past week.

#### Primary Maternal Assessments

The Consensus Sleep Diary [50] will collect subjective sleep, while actigraphy will be contemporaneously used to derive objective sleep data. The Pittsburgh Sleep Quality Index [51] will measure habitual sleep quality. The Edinburgh Postnatal Depression Scale [52,53] will be used to assess changes in the depressive symptoms over time. The Generalized Anxiety Disorder Scale-7 items [54] and the Perinatal Anxiety Screening Scale [55] will be used to assess anxiety symptoms over time.

Participants will have their blood drawn (up to 20 mL) at enrollment, 3 months post partum, and 6 months post partum at a Quest Diagnostics laboratory near them (Figure 1). Briefly, blood collection kits with ethylenediaminetetraacetic acid tubes will be mailed to participants with a requisition form and a laboratory directive (from Quest) that provides the Quest Diagnostics Patient Service Center instructions on how to collect and process the study kit. Blood samples will be shipped in a temperature-controlled fashion to the Psychoneuroimmunology in Pregnancy & Postpartum (PIPPI) laboratory at Weill Cornell Medical College for analysis. Measurements of circulating cytokines, stimulated cell assays, and flow cytometry analysis will be conducted to evaluate the role of immune dysregulation.

#### Secondary Maternal Assessments

The Insomnia Symptom Questionnaire [56] is a self-report instrument that identifies a clinically relevant case definition of insomnia consistent with widely used insomnia classification criteria. It has 13 items, which identify sleep symptoms, frequency, duration, and related daytime impairment. Scoring indicates positive or negative for insomnia. The Epworth Sleepiness Scale [57] will assess daytime sleepiness. The Flinders Fatigue Scale [58] will assess daytime fatigue.

#### Measures in Both Mothers and Infants

Actigraphy watches (Phillips/Respironics and ActiGraph, LLC) will be provided to the dyad each month to collect objective sleep data. Data collection and interpretation will be consistent with previous reports [59-61]. For infants, watches will be placed on the right ankle in accordance with suggested guidelines [61-63].

### Epigenetic Biomarker Testing

#### Blood Draw Collection

Upon enrollment, participants will be sent supplies from TruDiagnostic for blood collection, including a Tasso blood collection kit and a prepaid mailing kit to TruDiagnostic. Blood samples will be processed using the Illumina Human MethylEPIC beadchip. Methylation data for the *TTC9B*, *HP1BP3*, and *MS4A7* genes will be sent to [name] who will use the published algorithm for predicting postpartum depression risk to determine if the participant’s epigenetic methylation patterns are consistent with increased risk for postpartum depression. Participants will not be informed of their biomarker status, as we are still determining the clinical value of the biomarkers.

#### Immune Markers

Blood collection kits with ethylenediaminetetraacetic acid tubes will be mailed to participants with a requisition form and a laboratory directive (from Quest) that provides the Quest Diagnostics Patient Service Center instructions on how to collect and process the study kit. Aliquots of plasma and the second tube of whole blood will be shipped overnight to Weill Cornell Medicine. Peripheral blood mononuclear cell (PBMC) suspensions will be prepared within 24 hours of blood collection by low-density gradient centrifugation via Hermle Z300 (K#55085010) to avoid erythrophagy-related activation of the monocytes. PBMCs will be frozen and stored at –80 °C using 10% dimethylsulfoxide, thereby allowing all samples to be analyzed in parallel. Plasma will also be stored at –80 °C. In our prior studies, we have missing biological data (due to incomplete blood draws) in about 7% of the visits; we anticipate similar rates in this study.

#### Cytokine Analysis

Cytokine analysis will be performed under [name] supervision in the PIPPI laboratory at Weill Cornell Medicine. Plasma cytokines will be measured using the Meso-Scale Discovery Ultrasensitive Proinflammatory Multiplex kit (Meso Scale Diagnostics LLC) according to the manufacturer’s protocol in duplicate and read using the MS2400 imager (Meso Scale Diagnostics LLC). We will calculate the coefficient of variation for each woman’s replicates when both have concentrations above the limit of detection.

#### Cell Preparation and Stimulation

Maternal PBMCs will be thawed in Roswell Park Memorial Institute 1640 medium and distributed into three 24-well multiplates (5 × 10^5^ cells/well). Remaining cells will be aliquoted into two 5-mL culture tubes (2 × 10^6^ cells/tube). Cells will be maintained in a humidified atmosphere of 95% air/5% CO_2_ at 37 °C. After 24 hours, PBMCs in the 24-well plates will be treated with increasing concentrations of cortisol. Hydrocortisone stock solutions will be prepared by dissolving hydrocortisone in ethanol and then diluting with pyrogen-free sterile saline solution (NaCl 0.9%) to achieve equipotent final culture concentrations of 0.2 µg/mL (physiological plasma cortisol level) and 0.4 µg/mL (plasma cortisol level in high-stress status). PBMCs will be treated with a final cortisol concentration of 0, 0.2, and 0.4 µg /mL. Cells in the 5-mL culture tubes will be stimulated with phorbol myristate acetate (Sigma Aldrich) and ionomycin (Sigma Aldrich) in the presence of GolgiStop (Becton Dickinson) for 4 hours in 37 °C under a 5% CO_2_ environment to stimulate T-effector cells. Following the incubation periods, the supernatant from cortisol-stimulated cells will be collected and stored at –80 °C until assayed for interleukin (IL)-6, IL-10, IL-8, and IL-4 by using a commercial enzyme-linked immunosorbent assay. Cellular pellets will be resuspended and prepared for flow cytometry to assess the immune cell phenotype.

#### Flow Cytometry Analysis

Flow cytometry analysis will be performed on the BD LSRII instrument (BD Biosciences, 3 laser, 14 color) within the [name] laboratory adjacent to [name] PIPPI laboratory. Additional analyses, as necessary, will occur in the Weill Cornell Flow Cytometry Core, which houses a BD AriaII sorter, 5 laser (355, 405, 488, 561, 640) capable of 4-way sorting; a BD Influx sorter, 6 laser (355, 405, 445, 488, 561, 640) capable of 6-way sorting; a BD Fortessa analyzer, 5 laser (355, 405, 488, 561, 640) 20 parameter and a BD FACSCelesta analyzer, and 3 laser (405, 488, 561) 14 parameter. Panel one will include membrane staining markers and will be performed using thawed PBMCs. Stained cells will be analyzed by 8-color flow cytometry (with anti-CD3 BV786, anti-CD4 Pe-Cy7, anti-CD8 BV605, anti-CD14 antigen-presenting cell, anti-CD25 phycoerythrin, anti-CD16 PerCp-Cy5.5, anti-CD56 fluorescein isothiocyanate, and anti-CD19 BV421; Becton Dickinson). We will use a gating method to measure subsets of monocytes, lymphocytes, natural killer cells, T-cells, B-cells, CD4+ T helper cells, and CD8+ cytotoxic T cells. Samples stimulated with phorbol 12-myristate 13-acetate and ionomycin will be stained using a T-cell specific panel and analyzed by 8-color flow cytometry (with anti-CD3 BV786, anti-CD4 Pe-Cy7, anti-CD45RO BV605, anti-IFN-γ antigen-presenting cell, anti-CD25 PE, anti-FoxP3 PerCp-Cy5.5, anti-IL-4 fluorescein isothiocyanate, and anti-IL-17A BV421; Becton Dickinson).

### Process Measures

#### Treatment Expectation Questionnaire

An adapted version of the Treatment Expectation Questionnaire [64] will be administered at month 3 and month 6 to assess the mother’s expectations of benefits, satisfaction with condition, and fears. This measure asks about expectations regarding symptom relief, improvement, and benefits from using the specific bassinet. It allows for comparison of the impact of multidimensional expectations across different conditions. Open-ended comment boxes will be provided for mothers to report experiences, adverse events, or other comments.

#### Patient Adherence

Various items will be collected to determine patient adherence: (1) self-reported adherence assessed using an adapted survey checklist provided by [name], (2) self-report data on bassinet usage, (3) pictures of bassinet use by participants, and (4) comment boxes to explain nonadherence.

#### Additional Factors to Consider and Use as Covariates

These include (1) presence of spouse/partner and other children at home [36,65-67]; (2) type of feeding [68-70]; (3) infant variables such as acid reflux, colic, and gestational age; (4) consistency of bedtime routine [71-73] and when moved to a crib; (5) history of childhood trauma in the mother via the Childhood Trauma Questionnaire [74], as prior trauma is highly correlated with depressive episodes, especially in new mothers [75,76] and negatively affects sleep [77]; and (6) type of delivery, complications, or time spent in neonatal intensive care unit.

### Statistical Analysis

#### Power

Power analyses were performed using *P*<.05 (2-tailed) at .80 power, based on recommended guidelines [78-80]. The power analyses were conducted for each statistical technique to be pursued in aims 1 to 3: mixed (between-subjects and within-subjects) multivariate analysis of variance (MANOVA), mixed (between-subjects and within-subjects) analysis of variance, independent 2-sided *t* test, dependent 2-sided *t* test, correlation, and the mediational models involving structural equation modeling (based on the β coefficient). The pilot study collected similar measures from pregnant/postpartum women with a history of major depressive disorder who used SB or HALO TB. Hence, the power analyses were based on pilot sleep and mood data. Calculations revealed an average effect size across all postpartum timepoints (T1 to T6) between the treatment and control groups on the following measures: infant sleep (*d*=0.39), postpartum sleep quality (*d*=0.27), and postpartum depression (*d*=0.33). Based on these effect sizes, a sample size of 208 participants is needed for infant sleep, 434 participants for postpartum sleep quality, and 286 participants for postpartum depression to attain statistical significance. Thus, a final sample size of 393 participants will be targeted (allowing for an attrition rate of 15%).

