## Introduction

Postpartum mood and anxiety disorders (PMADs) are the most common and disabling complications of childbearing. They are often underdiagnosed and undertreated [1]. PMADs are recognized to seriously affect both mother and baby [2,3]. In fact, mental health conditions are a leading contributor to maternal morbidity, with suicide as a major cause of postpartum death. According to the Department of Defense, the number of females in the US military constituted 17.3% of the total force in 2021 [4]. Research indicates that the rate of PMADs in active-duty women can range from 20% to 26% [5-7], with slightly lower rates among military spouses at around 12.2%. Although these rates are similar to that reported in the civilian population (~10%-15%) [8-10], when other factors such as deployment are considered, the rates vary dramatically, reaching as high as 50% [11-16]. Women with spouses who are deployed have more frequent diagnoses of depressive disorders, sleep disorders, anxiety, acute stress reactions, and adjustment disorders compared to women without a deployed spouse. Despite these elevated risks, this segment of our population has been insufficiently evaluated as it pertains to PMAD risk and warrants further attention.

It is well appreciated that sleep disturbance is associated with both new and recurrent depressive and anxiety episodes in all populations, especially perinatal women [17-22]. Sleep disturbance often precedes the development of mood disorders [23,24]. Indeed, sleep issues lasting for at least 2 weeks increase the risk for the future development of mood disorders [25,26] and are a criterion for the diagnosis of depression in the Diagnostic and Statistical Manual of Mental Health Disorders, Fifth Edition, Text Revision (eg, major depressive disorder) [27]. Sleep disturbances, both in prevalence and severity, in military-affiliated women extend beyond what civilian women experience. Active-duty service members and their spouses experience unique stressors that often exacerbate sleep issues [28,29]. Despite this, there are limited empirical data regarding sleep disturbances among military-affiliated women.

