### Statistical Analyses for Immune Measurements

The initial statistical approach will include a descriptive cross-sectional analysis at each timepoint, both for quality assurance and to attain a better understanding of the distributions of the immune cell and cytokine profile variables for use in subsequent analyses, including the need for any transformations (ie, logarithmic transformation to symmetrize the residuals). Factor analysis will be employed as a means of data reduction to probe latent cytokine profiles reflected across the manifest indicators (eg, tumor necrosis factor-α, IL-6, IL-1β). We will first compare levels of a combined score of peripheral innate immune cytokines and frequency of maternal immune cells between women who do and do not develop PMADs in separate models to evaluate cross-sectional effects, employing a multivariable linear regression model to adjust for relevant covariates (eg, gestational age, BMI). Similar models will be repeated for maternal cytokines and innate cell recruiting factors as produced by the stimulated cells. Second, we will test whether the magnitude of group difference varies across the study period in a longitudinal analysis. We will fit a generalized linear population-average model estimated using generalized estimating equations with exchangeable working correlation structure to account for within-women correlation of mood measures. The model will include the relevant immune markers identified in the cross-sectional analyses, indicators for visit and group, as well as any relevant interaction terms (immune marker by group or immune marker by visit). The models will adjust for baseline severity of depressive symptoms and psychotropic medication use. Standard model checking will be performed, and the most parsimonious model will be selected based on the Akaike information criterion or quasi-likelihood information criterion for generalized estimating equations models. To test the within-group effects of severity of PMAD symptoms, the dichotomous group variable will be replaced by continuous Edinburgh Postpartum Depression Scale and Generalized Anxiety Disorder Scale-7 item scores in analytic models and restricted to only the subset of women with significant PMAD symptoms.

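### The 80% power statement covers aims 1 to 3, but no reported calculation supports hypothesis 3a, which compares unequal PMAD groups on immune markers; its power is unknown

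*Protocol article*

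**What the plan says.** The Power section of the protocol article sets a two-sided 5% level and 80% power and states: "The power analyses were conducted for each statistical technique to be pursued in aims 1 to 3". The techniques it lists are mixed MANOVA, mixed ANOVA, independent and dependent t tests, correlation, and structural equation mediation models. It then says: "Hence, the power analyses were based on pilot sleep and mood data". The effects it reports are smart-versus-traditional bassinet differences: d=0.39 for infant sleep, 0.27 for maternal sleep quality and 0.33 for depression. From these it derives that "a sample size of 208 participants is needed for infant sleep, 434 participants for postpartum sleep quality, and 286 participants for postpartum depression". The section targets 393 participants; the Abstract, Participants and Telephone Interview sections give 342.

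Hypothesis 3a, in the aims, is not about the randomised arms. It expects greater innate immune activity in women with PMADs than in women without. The section on immune measurements compares immune markers "between women who do and do not develop PMADs in separate models to evaluate cross-sectional effects", using multivariable linear regression and then GEE. It also replaces the group variable with continuous EPDS and GAD-7 scores, but in a model "restricted to only the subset of women with significant PMAD symptoms". The Mean Differences section separately assigns 3a to model 4, one of the treatment-versus-control by six-period MANOVAs.

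**The concern.** A reader would take the power statement to reach aim 3. Nothing reported matches hypothesis 3a in contrast, outcome, group sizes or method. The contrast is PMAD status, not bassinet. The outcome is immune, not sleep or mood. At the article's own PMAD rates the groups are far from equal. The regression and GEE models are not among the techniques listed.

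The risk lies in interpretation. A null PMAD comparison could be read as coming from a study sized at 80% for it, when moderate differences might well be missed. The continuous-score model, which could use more of the data, is confined to the smaller group.

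**Working it through.** **1. Reproducing the printed sizes.** For a 1:1 two-sample comparison, n per arm = 2(1.96+0.84)²/d², rounded up. Totals:

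| Outcome | d | Printed | Normal formula | t test |
|---|---|---|---|---|
| Infant sleep | 0.39 | 208 | 208 | 210 |
| Maternal sleep | 0.27 | 434 | 432 | 434 |
| Depression | 0.33 | 286 | 290 | 292 |

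The match is within about 2%. The article does not name its formula, so the t test is inferred from this agreement.

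**2. Women available for 3a.** Attrition of 15% and missing blood at about 7% of visits come from the Missing Data section.
- 342 × 0.85 × 0.93 ≈ 270
- 393 × 0.85 × 0.93 ≈ 311

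**3. Split by PMAD status.** The article gives 12.2% for spouses and up to 26% for service women. For 270 women the split is 33 vs 237 to 70 vs 200. For 311 women it is 38 vs 273 to 81 vs 230.

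**4. Detectable difference at 80% power.** d ≈ 2.80/√(N·p·(1−p)). This needs no assumed immune effect.
- N=270: 2.80/√28.9 ≈ 0.52 at 12.2%; 2.80/√51.9 ≈ 0.39 at 26%
- N=311: 2.80/√33.3 ≈ 0.49 at 12.2%; 2.80/√59.8 ≈ 0.36 at 26%

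**5. Illustrative power at d=0.33.** This value is borrowed from the bassinet effect on depression and is an assumption. Unequal-group t test, two-sided 5%:

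| Women analysed | 12.2% | 20% | 26% | 50% |
|---|---|---|---|---|
| 270 | 0.42 | 0.58 | 0.66 | 0.77 |
| 311 | 0.48 | 0.64 | 0.72 | 0.83 |

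The 50% column uses the highest rate that the Introduction cites once factors such as deployment are considered. For 80% power at d=0.33, about 673, 450 and 375 analysable women would be needed at 12.2%, 20% and 26%.

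**6. Does 80% hold for the bassinet comparisons?** Completers are 393 × 0.85 ≈ 334 or 342 × 0.85 ≈ 291.

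| Outcome | Needed | Power, 334 | Power, 291 |
|---|---|---|---|
| Infant sleep (d=0.39) | 208 | 0.94 | 0.91 |
| Depression (d=0.33) | 286 | 0.85 | 0.80 |
| Maternal sleep (d=0.27) | 434 | 0.69 | 0.63 |

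Maternal sleep does not reach 80% at either N, so the statement cannot simply be narrowed to all three bassinet outcomes.

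**The case against.** The strongest reply is that the section speaks of techniques, not hypotheses. It discloses its sleep and mood basis and never says that 3a has 80% power. A condensed article may also omit a calculation that exists elsewhere. This stands as a limit on wording: the article shows that no aim 3 calculation is reported, not that none was done. It does not rescue the statement, which names aim 3 while its list omits the regression and GEE models used for 3a.

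A reader might infer that 3a has 42% to 66% power. The documents do not support that. They give no immune effect; d=0.33 is a treatment effect on depression; and that range uses N=342 rather than the Power section's 393. The PMAD share is also uncertain both ways. Excluding women with a current disorder could lower it, while deployment could raise it towards 50%, where the gap largely closes. Covariate adjustment and repeated measures could shift power too.

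It is also fair that the symptom-subset model has a stated purpose, the effect of severity within the PMAD group, and that hypothesis 3a is worded as a case comparison. Replacing that contrast as the main test would be a debatable trade-off. Adding an all-women analysis beside it is not open to that objection.

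**Conclusion.** The point holds as a mismatch between the scope of the power statement and what is reported for it; the three printed sizes themselves reproduce. Power for hypothesis 3a is unknown. At PMAD rates of 12.2% to 26% and the stated losses, a simple two-group comparison detects d of about 0.52 to 0.39 (N=342) or 0.49 to 0.36 (N=393) with 80% power. If the effect were 0.33, power would be about 0.42 to 0.66 or 0.48 to 0.72, and higher if the PMAD rate approached 50%. These figures assume an unadjusted single-visit comparison, with attrition and missing blood applied in turn.

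**What to change.** - **Power section:** limit the 80% statement to the bassinet outcomes whose required N is met after attrition, namely infant sleep and depression. Remove aim 3 from it. Give the detectable difference for 3a at the expected PMAD split and at whichever N is final.
- **Immune analysis section:** keep the PMAD versus no-PMAD contrast, reported with its confidence interval. Add, as a supporting analysis, the association of immune markers with continuous EPDS and GAD-7 in all women with blood. The symptom-subset model can stay for its own question.
- **Mean Differences section:** reconcile model 4, which is built on treatment versus control over six periods, with the PMAD comparison in the immune section, so that 3a has one stated main analysis.

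The cost is wording and one more supporting analysis, with no new participants or data. The downside is a less favourable power statement for aim 3.

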**Methods:**

This study is a 6-month, parallel-arm, randomized controlled trial. Pregnant women (N=342) in the third trimester will be randomized at 1:1 ratio to use a smart bassinet (SB) or a standard commercially available bassinet (HALO BassiNest Swivel Sleeper 3.0; traditional bassinet [TB]) for up to 6 months after delivery. Participants will have their infants sleep in the bassinet, complete monthly web-based questionnaires, and record sleep data with diary and actigraphy for both the participants and their infants for 1 week each postpartum month. Blood samples will also be collected at baseline (late pregnancy) and at 3 months and 6 months post partum to assess immune functioning. The primary outcomes for this study will be postpartum mood (depressive and anxiety symptoms) and infant and maternal sleep. In addition, we are evaluating whether SB has a significant impact on immune functioning—a marker that physiologically connects sleep and mood symptoms.

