#### Telephone Interview and Screening

Participants who meet initial inclusion criteria and have completed the consent and baseline questionnaires will be contacted for a telephone interview to assess further eligibility. The interview will contain items of the Structured Clinical Interview for Diagnostic and Statistical Manual of Mental Disorders-5-Clinical Version [42] and the Structured Clinical Interview for Sleep Disorders-Revised [43]. Eligible participants will be randomly assigned to either SB group or TB group. The SB will be shipped to the participants and returned after M6 at no expense to them. TB group participants will be shipped a standard bassinet (HALO BassiNest Swivel Sleeper) to keep. Mother-infant dyads (up to N=342) will be randomly assigned to conditions by using a random number generating program found on a widely used and reputable website [44]. We will perform 1:1 randomization. Variability in the length of bassinet usage may be impacted by size of infant, parental preference, or infant temperament. However, data will be collected through 6 months post partum.

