### Missing Data

Attrition in our prior studies has been approximately 15%, and we have accounted for that in our planned sample size. In addition, in our prior studies, we have missing biological data (due to incomplete blood draws) in about 7% of the visits; we anticipate similar rates in this study, which will use the same approach. Given the prospective nature of our study, we will carefully evaluate missingness. If identified, we will employ one of the two strategies to handle missing data. The first approach relies on a technical assumption of missing at random and involves inclusion of covariates related to missingness in all analyses. Full information maximum likelihood performs well under ignorable missing data conditions such as missing at random. A second strategy we will use is multiple imputation. Although this has the potential to yield biased estimates dependent on the nature of missingness [97], we will employ this approach to implement sensitivity analysis under plausible assumption of missing not at random to examine the robustness of our inference [98].

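### The planned total is given as 342 and as 393, and neither reaches the 434 that the plan itself requires for maternal sleep quality, a primary outcome

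*Protocol article*

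**What the plan says.** Three places in the protocol article give 342. The abstract (Methods) has "Pregnant women (N=342) in the third trimester will be randomized at 1:1 ratio". The Participants section recruits the same number nationwide. Telephone Interview and Screening makes it a ceiling: "Mother-infant dyads (up to N=342) will be randomly assigned to conditions".

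The Power section gives a different total. Its criterion is "Power analyses were performed using *P*<.05 (2-tailed) at .80 power". The pilot effect sizes, described as averages over the postpartum timepoints, are "infant sleep (*d*=0.39), postpartum sleep quality (*d*=0.27), and postpartum depression (*d*=0.33"). The requirements drawn from them are "208 participants is needed for infant sleep, 434 participants for postpartum sleep quality, and 286 participants for postpartum depression". The next sentence concludes: "Thus, a final sample size of 393 participants will be targeted (allowing for an attrition rate of 15" per cent).

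The Missing Data section adds: "Attrition in our prior studies has been approximately 15%, and we have accounted for that in our planned sample size".

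The abstract lists maternal sleep among the primary outcomes, next to postpartum mood and infant sleep. Maternal sleep is the subject of hypothesis 1b.

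**The concern.** There are two separate problems.

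First, the trial has two planned totals. Nothing in the article calls 342 a completer number or otherwise connects it to 393. Recruitment began in January 2025, so the team is enrolling towards a target that the document does not settle.

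Second, the total is presented as following from three requirements, the largest of which is 434. A total that already allows for attrition cannot be smaller than a requirement it is meant to satisfy. The article does not say that depression alone sets the size, or that lower power is accepted for maternal sleep quality. As written, the 80% criterion appears to cover all three outcomes. A null result on hypothesis 1b would then be hard to interpret, because the stated power would not be the power the trial had.

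**Working it through.** **Inputs (Power section).** Two-sided alpha 0.05, power 0.80, 1:1 allocation; d = 0.39 (infant sleep), 0.27 (maternal sleep quality), 0.33 (depression); attrition 15%.

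**Step 1: reproduce the three requirements.** Two-sample comparison of means, n per arm = 2(1.960 + 0.842)²/d² = 15.70/d², rounded up and doubled. The exact t test adds about one woman per arm.

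| Outcome | d | Stated | Normal approx. | Exact t |
|---|---|---|---|---|
| Infant sleep | 0.39 | 208 | 208 | 210 |
| Maternal sleep quality | 0.27 | 434 | 432 | 434 |
| Depression | 0.33 | 286 | 290 | 292 |

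All agree within 3%, and 286 is within the rounding of d (d = 0.332 gives 2 x 143 = 286). One-sided versions do not fit (164, 340, 228). The printed requirements are those of a plain two-group comparison.

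**Step 2: try to reproduce 393.**

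| Base | / 0.85 | x 1.15 |
|---|---|---|
| 208 | 245 | 240 |
| 434 | 511 | 500 |
| 286 | 337 | 329 |
| mean of the three, 309.3 | 364 | 356 |

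None gives 393. The match found is 342 x 1.15 = 393.3, but 342 does not appear in the Power section. In turn, 342 is close to the depression requirement with attrition included: 290/0.85 = 341.2, or 342 in equal arms.

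**Step 3: power at each candidate number (exact t test).** Evaluable numbers after 15% complete loss: 342 x 0.85 = 291 and 393 x 0.85 = 334.

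| Randomised | Evaluable | Infant sleep | Maternal sleep quality | Depression |
|---|---|---|---|---|
| 342 | 291 (15% lost) | 91% | 63% | 80% |
| 342 | 342 (no loss) | 95% | 70% | 86% |
| 393 | 334 (15% lost) | 94% | 69% | 85% |
| 393 | 393 (no loss) | 97% | 76% | 90% |

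Hand check for 291 and d = 0.27: 0.27 x √291 / 2 − 1.96 = 0.34, and Φ(0.34) = 0.63.

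The effect detectable with 80% power is d = 0.330 with 291 evaluable and 0.307 with 334, against the assumed 0.27. Keeping 434 evaluable after 15% loss needs 434/0.85 = 510.6, so 511 randomised (512 for equal arms).

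**Step 4: sensitivity to repeated measures.** Assume that d = 0.27 is a per-month effect, that the arm effect is averaged over six months, and that all between-month correlations equal ρ. The variance is then multiplied by (1 + 5ρ)/6. The article gives no ρ, so a range is shown for about 291 evaluable.

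| ρ | Power | Evaluable N for 80% |
|---|---|---|
| 0.5 | 85% | 254 |
| 0.6 | 80% | 290 |
| 0.7 | 75% | 326 |
| 0.8 | 71% | 362 |
| 0.9 | 67% | 398 |

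**The case against.** **Repeated measures.** The strongest defence is that the main analysis is a mixed 2 x 6 model, and the Power section says that each planned technique had its own power analysis. With six monthly measurements, 291 evaluable women could give 80% or more for maternal sleep quality if the between-month correlation is about 0.6 or lower. This stands as a condition on the finding: the shortfall is certain only on the t-test basis. It does not remove the finding. The only requirement printed for this outcome is 434, which is the t-test figure; no correlation is stated; and at 0.8 or 0.9 the shortfall remains. If d = 0.27 already describes the six-month average, averaging gains nothing.

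**Attrition is not complete loss.** The plan provides for multiple imputation and full information maximum likelihood, so women who leave late still contribute. This is fair, and it is why ranges are given. The upper ends, 70% and 76%, assume no loss at all and are still below 80%.

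**A stronger reading that the article does not support.** A reader might infer from 342 x 1.15 = 393.3 that the 15% allowance was calculated the wrong way, or that 342 omits attrition and so contradicts the Missing Data section. Neither is established. The derivation of 393 is not shown, and the first inference needs 342 to be the evaluable number, whereas the article calls it the number recruited or randomised. Because 342 also fits 290/0.85, it may already include a correct allowance for depression, with 393 adding attrition a second time. Nor would such an error explain the shortfall: 342/0.85 = 403, which is still below 434.

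**Conclusion.** The point holds on what the article prints. The totals 342 and 393 conflict, 393 does not follow from any of the three stated requirements, and both totals are below the stated 434 for a primary outcome. On the two-sample basis that reproduces 434, the criterion of 80% is missed by 10 to 17 percentage points with 342 randomised and by 4 to 11 with 393. Only maternal sleep quality is affected.

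The size of the shortfall rests on three assumptions: the pilot d of 0.27, the single-comparison t test, and loss between none and 15% complete. A repeated-measures calculation could reduce or remove it, depending on a correlation that the article does not give. The article does not show which of 342 and 393 is intended, or that the attrition step itself is wrong. No power shortfall has been calculated for the mediation hypothesis (2b), so none is claimed.

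**What to change.** 1. State one randomised total in the abstract, Participants, Telephone Interview and Screening, and Power sections, and show its derivation. Apply attrition once, as n/(1 − 0.15), and say what n is.
2. Name the outcome that sets the sample size.
3. Restate power for each primary outcome at that total. With 342 randomised and 15% lost, this is about 91% (infant sleep), 63% (maternal sleep quality) and 80% (depression); with 393, about 94%, 69% and 85%. Say plainly that maternal sleep quality is below 80% on the t-test basis, and that 80% would need about 511 randomised.
4. Alternatively, justify the chosen total with the power of the planned repeated-measures arm effect. State whether d is per month or for the six-month average, and give the assumed between-month correlation and its source.

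Disclosure costs only wording and a less favourable stated power for one outcome. If 393 is the intended total, it means 393 − 342 = 51 more women than the recruitment sections plan. Powering maternal sleep quality on the t-test basis would mean 511 − 342 = 169 more. That choice is the sponsor's, and the inconsistency can be resolved without it.
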